### Plans for collection, laboratory evaluation, and storage of biological specimens for genetic or molecular analysis in this trial/future use {33}

Stool and blood samples will be collected at site from the participant and processed. Then, aliquoted stool, serum, and plasma will be stored at − 80 °C in the freezer located at site until further analysis for the same purpose of the study objectives. Additional samples from participants who provided Optional Specimen Consent for biobanking and genetic testing will be kept up to 15 years, until they are used up for future studies, yet to be determined, or destroyed.

### Statistical methods

#### Statistical methods for primary and secondary outcomes {20a}

Descriptive statistics will summarize all study variables. Prior to analysis, numerical variables with skewed distribution will be transformed (e.g., log_2_ or cubed root) or a comparable nonparametric test will be used. Between-group comparison of primary and secondary outcomes will be performed at baseline and two consecutive time points independently using unpaired *t*-tests (comparing two groups) or analysis of variance (three groups) and chi-square tests for numerical and categorical data, respectively. Impact of the three interventions on IR (HOMA-IR, primary endpoint) over time will be compared using linear mixed models, after adjusting for relevant confounders, including pubertal stage if any statistically significant difference is observed between treatment groups at baseline. OTU relative abundance will be compared between treatment groups. Statistical analyses for gut microbiota community composition will include principal coordinates analysis and canonical correlation. Linear discriminant analysis Effect Size [78] and multivariate association with linear models will be used to identify specific OTUs that differentiate the treatment groups. Mediation modeling will be employed to provide further insights on possible casual pathways to explore whether the gut microbiota may play a causal or mediation role in the physiological effects detected [79]. Treatment responders versus non-responders will also be evaluated. We will characterize the ecological differences prior to the intervention, and then the individualized response to the intervention in order to assess the role of the microbiome in the host’s metabolic response to the intervention. For this analysis, we will apply a machine learning approach called partition around medoids clustering [80]. Separate models will be estimated for secondary endpoints, which are exploratory, but nevertheless important. Intervention types and times will be included as fixed effects in linear mixed models. Pearson or Spearman correlation coefficients will be computed between changes in gut microbiome composition/function and insulin resistance, hormones, metabolites, and inflammatory markers.

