### Outcomes {12}

The primary outcome of this study is a change in IR, as estimated by HOMA-IR, between baseline, 6, and 12 months. The secondary outcomes of this study include changes between baseline, 6, and 12 months in (1) the Matsuda, insulinogenic, and oral disposition indices as determined by OGTT; (2) weight, BMI percentile and *z*-score, and body composition (fat mass, fat-free mass, and ratio of fat mass to fat-free mass); (3) QoL and perceived hunger and satiety; (4) fasting metabolic (glucose, adiponectin, lipids, and OGTT) and satiety markers (acylated ghrelin, PYY, GLP-1, and leptin); (5) measures of systemic inflammation (C-reactive protein, interleukin 6, and TNF-α) and gut barrier integrity (lipopolysaccharide-binding protein [LPB] and fecal calprotectin); and (6) gut microbiome composition and functions (fecal microbiome composition, fecal SCFAs and bile acids, and targeted plasma metabolomics [amino acids, branched chain ketoacids, acylcarnitines, ceramides, trimethylamine *N*-oxide, choline, and betaine]).

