### Participant timeline {13}

#### Sample size {14}

Our primary outcome is IR as estimated by HOMA-IR. Based on a recent study where the effect size of MET on HOMA-IR among pubertal participants was 0.75 [49], we estimated a sample size of 29 per arm, which will give us 90% power to find any significant post-intervention difference between arms at 5% significance level. Additionally, a percentage of change and 95% confidence interval for HOMA-IR after PGX from Pal et al. [50] resulted in an effect size of 0.86, rendering a sample size of 26 per arm. We expect a greater response in the combination therapy; for this reason and considering 26 per arm as feasible, and 15% attrition rate during follow-up, we estimated a total of 90 participants over the 3 arms.

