## Discussion

This study will compare the metabolic benefits of fiber with those of metformin in adolescents with obesity, determine if metformin and fiber act synergistically to improve IR, and elucidate whether the metabolic benefits of metformin and fiber associate with changes in fecal microbiota composition and the output of health-relevant metabolites. The study will thereby assess the relationship between therapeutic intervention(s) and putative mechanisms that are hypothesized to underlie the clinical effects. Overall, we predict that the combination of MET and fiber will have a synergistic effect, being more effective than MET or fiber alone at 12 months in improving IR and BMI in the adolescents with obesity. We further predict that these metabolic benefits will be associated with changes in gut microbial composition and metabolic functions (assessed by 16S rRNA gene amplicon sequencing, fecal SCFAs and bile acids, and targeted plasma metabolomics) and measures of systemic inflammation and intestinal barrier function (assessed by plasma cytokine, LBP, and fecal calprotectin). If successful, our proposed combination therapy may help to interrupt the cycle of weight gain and IR, thereby reducing the risk for developing T2DM, a worldwide public health concern, in adolescence and adulthood.

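### HOMA-IR is the primary outcome at both 6 and 12 months and is tested visit by visit and again in a mixed model, with no deciding time point or test named

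*Protocol article*

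**What the plan says.** Outcomes {12} of the protocol article gives the primary outcome with two follow-up visits: "The primary outcome of this study is a change in IR, as estimated by HOMA-IR, between baseline, 6, and 12 months". Neither visit is ranked above the other.

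Statistical methods for primary and secondary outcomes {20a} gives two analyses of this endpoint.
- Visit-wise tests: "Between-group comparison of primary and secondary outcomes will be performed at baseline and two consecutive time points independently". For numerical outcomes the tests named are a t-test where two arms are compared and ANOVA where all three are.
- A longitudinal model: "Impact of the three interventions on IR (HOMA-IR, primary endpoint) over time will be compared using linear mixed models". On the model terms, the section says: "Intervention types and times will be included as fixed effects in linear mixed models". It names no treatment-by-time term and no contrast.

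Sample size {14} claims "90% power to find any significant post-intervention difference between arms at 5% significance level". It does not divide the level between visits, tests or pairs of arms.

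The Discussion predicts that the combination will do best, "being more effective than MET or fiber alone at 12 months in improving IR and BMI". That is the only place where the expected superiority over each monotherapy is tied to a visit. Interim analyses {21b} states that there are none, so no alpha-spending rule covers the 6-month comparison.

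**The concern.** The text leaves several routes to a statement that the primary outcome was met: a 6-month test, a 12-month test and a mixed-model test, all on the same endpoint and each at 5%. If the route can be chosen after the results are known, the 5% level no longer describes the primary claim. An effect present at 6 months and gone by 12 months could also be reported as success on a question that the Discussion poses at 12 months.

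The time point belongs to the definition of the primary outcome. An analysis plan that later picked one visit would be narrowing an outcome already published with two.

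**Working it through.** **Inputs from the article.** Three arms, 1:1:1 (Trial design {8}); 5% level and 26 per arm (Sample size {14}). With 30 enrolled per arm and 15% attrition, 30 × 0.85 = 25.5, so 26 is a fair number of completers. Whether the stated sample size delivers its stated power is a separate matter and does not affect this check.

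**Assumptions, not in the article.** Equal correlation ρ between the three visits, with a range of 0.4 to 0.8; normal data; no true difference between arms; and any one p < 0.05 counted as a positive primary result.

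**Plan's own figure.** A single omnibus ANOVA at 12 months gave 4.8% to 5.0% in 40,000 simulated null trials. One prespecified test therefore does hold the stated 5%.

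**Bounds if the tests were independent.**
- Two tests: 1 − 0.95² = 9.75%.
- Three tests: 1 − 0.95³ = 14.3%.

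**Simulated rates of at least one significant omnibus test, 26 per arm.**

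| Tests combined | ρ = 0.4 | ρ = 0.6 | ρ = 0.8 |
|---|---|---|---|
| Raw values at 6 and 12 months | 9.3% | 8.5% | 7.9% |
| Raw values at both visits, plus mean of follow-up values | 10.1% | 9.2% | 7.9% |
| Change at both visits, plus mean change | 9.7% | 9.6% | 10.0% |
| Raw values at both visits, plus mean change | 13.3% | 12.9% | 12.4% |

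Change scores at the two visits alone gave 8.8% to 9.4% for ρ from 0 to 0.9. The mean follow-up value or mean change stands in for a mixed-model test of the treatment effect averaged over visits. Rows come from separate simulation runs, so differences of a few tenths of a point carry no meaning.

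**Why the scale matters.** Under equal correlation and equal variance:
- A raw visit value correlates with the raw follow-up mean at √((1 + ρ)/2), which is 0.84, 0.89 and 0.95 for the three values of ρ.
- A change score correlates with the mean change at √(1.5/2) = 0.87, whatever ρ is.
- A raw visit value correlates with the mean change at only √((1 − ρ)/6), which is 0.32, 0.26 and 0.18.

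On one scale the third test largely repeats the first two and adds little. Across scales it is close to a fresh test, and the rate moves towards the 14.3% bound.

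**Does naming 12 months alone restore 5%?** Only if one omnibus test decides. With unadjusted t-tests at a single visit, the rate is about 9% if either comparison of the combination with a monotherapy may count, and about 12% if any of the three pairs may count.

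**The case against.** The strongest reply is that the article does contain a main analysis. The mixed-model sentence is the one that attaches a method to HOMA-IR as primary endpoint, and secondary endpoints get separate models that are labelled exploratory. The visit-wise sentence is generic: it covers all outcomes, numerical and categorical, and includes baseline, where no treatment effect can exist. It can be read as description. Nor is the Discussion the only pointer to 12 months. The sample size section refers to a difference after the intervention, the intervention lasts 12 months, and the background frames the aim over 12 months. Finally, this is a condensed article, and an analysis plan that is not shown may fix the contrast.

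Much of this stands. It rules out saying that the trial's type I error is 8% to 13% as a fact. A reader might infer that each significant result counts as success, but no section says so. A reader might also take all three pairwise t-tests at both visits, which gives about 18% to 22% unadjusted at ρ from 0.4 to 0.8. That needs a further assumption, because the article names ANOVA for three groups.

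The reply does not remove the ambiguity. The visit-wise sentence expressly includes primary outcomes. Even if the mixed model decides, its contrast and time point are open, and the outcome definition still lists two visits on equal terms.

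**Conclusion.** The point holds as a defect of specification: a primary outcome at two visits, overlapping tests of it, one undivided 5% level, and no deciding time point or test.

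Its size is conditional on any one significant omnibus result being claimed as primary. On that assumption, with 26 per arm and an assumed correlation of 0.4 to 0.8, the false-positive rate is about 8% to 10% on one scale. It reaches about 12% to 13% only when raw-value visit tests are combined with a change-from-baseline model test. If the mixed model is in fact the sole deciding analysis with one prespecified test, the rate is about 5% and only the wording is at fault. Should-fix.

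**What to change.** In Outcomes {12} and in Statistical methods {20a}:
1. State that the single primary analysis is the 12-month comparison of change in HOMA-IR from the linear mixed model with a treatment-by-time term. This agrees with the prediction in the Discussion.
2. State the deciding arm comparison. One option is the three-arm omnibus test at 12 months, with pairwise comparisons only if it is significant. With three arms this keeps the family error at 5%, because once any arm differs at most one pairwise null can still be true. The other option is the combination versus each monotherapy with an adjustment such as Holm, where the smaller p-value is first compared with 2.5%. This follows the stated prediction more directly.
3. Label the 6-month contrast and all visit-wise t-tests and ANOVAs secondary or descriptive.

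The cost is a few sentences, with no added participants or visits. The Trial status section says that recruitment had not started under that protocol version, so on the article's own account the choice could be made before any outcome data. The downside is that an effect seen only at 6 months can no longer be claimed as the primary result. The Holm option also gives up some power per comparison relative to unadjusted testing.

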## Assignment of interventions: allocation

### Sequence generation {16a}

After having provided written informed consent/assent, participants will undergo a baseline assessment and be randomized to one of the three intervention groups A, B, and C (i.e. MET, FIBER, MET + FIBER) via computer-generated numbers and stratified by age and sex, using the adaptive (dynamic) randomization (Step 2, Fig. 3). Each group will be also randomly allocated to one of three intervention arms of MET, FIBER, and MET + FIBER (Step 3, Fig. 3). Staff who completed Steps 2 and 3 will be different and will be blinded to the other step. Stratification will be based on four sex/age categories of male 12–15 years old, female 12–15 years old, male 16–18 years old, and female 16–18 years old.

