## Data collection and management

### Plans for assessment and collection of outcomes {18a}

Study visits will be conducted at the Human Nutrition Research Unit, a state-of-the-art facility supporting leading nutrition intervention research at the UofA. Participants will be seen at baseline (visits 0 and 1), 3, 6, and 12 months, and a phone follow-up will be completed at 1 and 9 months (Table 1). The 12-month duration of the intervention will assess both short- and longer-term effects of the combined FIBER plus MET intervention. At visit 0, and after obtaining informed consent/assent, baseline assessments will be conducted, including demographics, medical history, physical exam, sexual maturation (Tanner stage), anthropometrics, and body composition; in addition, participants will complete QoL, gastrointestinal tolerance, and 7-day physical activity questionnaires. During this visit, research staff will provide to the participants a 3-day food record (to assess dietary intake), Satiety Labeled Intensity Magnitude (SLIM) and bowel habit (Bristol stool chart) questionnaires, and stool sample collection kits to be completed at home and brought to visit 1 (day 0); this visit will occur within the following 10 days after visit 0. At visit 1, fasting blood samples will be withdrawn, and an OGTT will be completed. Once baseline assessments are completed, participants will be randomly assigned to one of the three study groups and the respective study intervention will be delivered.

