By employing targeted fecal and plasma metabolomics with fecal microbiota sequencing, we can identify changes in metabolite production that correlate with modifications of the gut microbiota. This systematic analysis of the gut microbial community may result in the identification of baseline microbiota configurations or metabolites that predict effects of MET and/or fermentable fibers and could, therefore, be used to enhance clinical responses with personalized therapies. Such novel biomarkers might also be relevant for predicting the future risk of developing metabolic abnormalities associated with childhood obesity. Our novel approach will inform the development of future microbiome-targeted pharmaceutical and prebiotic therapies, including the possible implementation of long-term, multicenter microbiome-targeted intervention studies aimed at improving health outcomes in childhood obesity. Finally, the goal of the research team is to provide a basis for using the gut microbiome as a window to improve the assessment and treatment of metabolic abnormalities in children with obesity.

While the high dietary fiber dose and 12-month intervention period are considered strengths of study, and potentially necessary for attaining reliable and sustained health benefits linked to fiber [85], both variables may impact protocol adherence and attrition throughout the intervention. To partially mitigate this, regular clinic visits, phone calls, emails, and text messages will occur to ensure the participants’ engagement and encourage protocol adherence. We will also monitor adherence through self-documentation (dosing journal) and collecting all unused study products. Another study limitation is that features of the participant’s lifestyle (i.e., diet and physical activity) remain uncontrolled. While this “real life” approach greatly improves the generalizability of study findings, as is often the case, intentional or unintentional lifestyle changes can occur that independently improve IR and BMI. To minimize these effects, participants will be encouraged to follow the study protocol without intentional lifestyle changes. Additionally, 3-day food records and physical activity questionnaires will be completed at baseline and throughout the dietary intervention to establish deviations from baseline, which will be incorporated and controlled through statistical analysis.

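### Adjustment of the primary model for pubertal stage hinges on a baseline significance test, and the sex/age randomisation factors are not named in the model

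*Protocol article*

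**What the plan says.** All references are to the protocol article.

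- **Statistical methods {20a}**, primary endpoint: the arms are compared on HOMA-IR over time by linear mixed models, "after adjusting for relevant confounders, including pubertal stage if any statistically significant difference is observed between treatment groups at baseline".
- The same section plans tests at baseline: "Between-group comparison of primary and secondary outcomes will be performed at baseline and two consecutive time points independently". Its only statement of model terms is "Intervention types and times will be included as fixed effects in linear mixed models".
- **Sequence generation {16a}**: participants are allocated "stratified by age and sex, using the adaptive (dynamic) randomization", and "Stratification will be based on four sex/age categories" (two age bands by sex). No section places these factors in the primary model. Additional analyses {20b} uses age and sex for subgroups within arms.
- **Plans for assessment {18a}**: Tanner stage is recorded for everyone at visit 0, before randomisation.
- **Discussion**: departures from baseline diet and activity are to be recorded, "which will be incorporated and controlled through statistical analysis", with no baseline test attached.

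**The concern.** A baseline significance test in a randomised trial tests a hypothesis already known to be true, namely that the arms come from one population. Its result says nothing about whether a covariate predicts the outcome, which is what decides whether adjustment helps. Followed as written, the rule normally discards the one covariate that the authors single out as relevant. It also leaves the form of the primary model open until baseline data have been compared by arm.

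Factors used to balance the allocation raise a related difficulty. Balancing removes their contribution to the true variability of the treatment contrast. A model without them still counts that contribution as residual noise, so the standard error is too large. An imbalance test will hardly ever bring such factors in, because the allocation has made them balanced.

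What is at stake is precision and a fixed primary model, in a trial with about 25 completers per arm.

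**Working it through.** **Inputs from the protocol.** Standardised effect 0.75, 5% level, 15% attrition (Sample size {14}); 30 per arm (Trial design {8}). Completers per arm: 30 × 0.85 = 25.5.

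**Assumptions.** Two-sided testing (sidedness is not stated); the baseline test is also at 5%; R², the share of residual variance explained by Tanner stage and the sex/age categories, is varied because the protocol gives none.

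**The plan's own figure.** The protocol gives no figure for the covariate rule. Its sample size is 29 per arm for an effect of 0.75 at 90% power. A two-sided 5% t-test has 80.1% power at 29 per arm and needs 39 per arm for 90%. That mismatch is a separate matter. It is noted only because it explains why the starting power below is not near 90%.

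**Step 1: how often the rule admits a covariate.** Under simple randomisation a 5% test is positive with probability 0.05 whatever the covariate's prognostic value, so a given covariate is omitted with probability 0.95. Simulation with 78 completers in three arms, 4,000 runs per setting and an assumed age–Tanner relation gave:

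| Allocation | Tanner selected | Age or sex selected | Nothing selected |
|---|---|---|---|
| Simple | 5.0–5.4% | 4.6–5.8% each | 86–88% |
| Dynamic within the four sex/age strata | 0.6–0.9% | never | about 99% |

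Stratification makes selection rarer still, because Tanner stage follows age.

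**Step 2: effect on the test.** In the same simulation (one follow-up time point, total assumed R² of 0.3 to 0.4, dynamic allocation):

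| Analysis | Type I error (nominal 5%) | Power at 0.75 |
|---|---|---|
| No covariates | 2.4–2.9% | 77% |
| Covariates by baseline test | 2.3–2.9% | 77% |
| Tanner, age and sex always in | 5.0–5.5% | 89–93% |

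The Monte Carlo standard error at 5% is √(0.05 × 0.95 / 4000) = 0.34 percentage points, so 5.5% is compatible with the nominal level, while 2.3–2.9% is clearly below it. In this simulation the test-based rule performs like no adjustment.

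**Step 3: gain over a range of R².** Adjustment multiplies the residual SD by √(1−R²), so the effective standardised difference is d′ = 0.75/√(1−R²). The noncentrality is d′ × √(25.5/2), with 2 × 25.5 − 2 = 49 degrees of freedom and critical value 2.010.

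| R² | d′ | Noncentrality | Power |
|---|---|---|---|
| 0 | 0.750 | 2.678 | 75% |
| 0.1 | 0.791 | 2.823 | 79% |
| 0.2 | 0.839 | 2.994 | 84% |
| 0.3 | 0.896 | 3.201 | 88% |

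These are two-group approximations for one pairwise contrast and ignore the few degrees of freedom spent on covariates.

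**The case against.** Five objections deserve weight.

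- **The condition may attach to pubertal stage alone.** The sentence can be read that way. The other relevant confounders are then merely unnamed, and the sex/age factors are neither excluded nor made conditional. This stands. The wording about any significant difference favours the wider reading but does not settle it. On either reading the rule applies in full to pubertal stage.
- **Not listing strata is detail left to the full protocol or analysis plan.** This is fair for the strata taken alone. It does not cover the conditional rule, which is printed and which an analysis plan following this text would inherit.
- **Baseline HOMA-IR.** A reader might infer that the strongest predictor is thrown away and that naming it would lift power from 75% to 86–96%, the result of a baseline–follow-up correlation of 0.5 to 0.7. The documents do not support this. Outcomes {12} defines change across baseline, 6 and 12 months, and time is a fixed effect, so baseline may already be in the model as a time point. Against a change-from-baseline contrast with variance 2(1−r), r = 0.7 gives 92% versus 96%, not 75% versus 96%. No gain is claimed here.
- **Harm to the type I error.** A reader might infer that a data-driven model inflates false positives. The simulation shows the opposite: the test is conservative. Since the rule almost never selects anything, the p-value would seldom change because of it.
- **Adjustment is not uniformly conditional.** Diet and activity departures are to be controlled with no baseline test. This stands, and it limits the point to baseline covariates.

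**Conclusion.** The point holds for the rule as printed. Making adjustment for pubertal stage depend on a significant baseline difference selects on chance imbalance, and it omits the covariate at least about 95% of the time. With allocation stratified on sex and age, the simulated figure is about 99%. The sex/age factors are not named in the primary model. If they are prognostic and left out, standard errors are too large and the test is conservative.

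The size of the loss is an assumption, because no passage gives a prognostic strength for Tanner stage, age or sex. Over R² of 0.1 to 0.3 the forgone power is about 4 to 13 percentage points from a base of 75%; at R² of 0 nothing is lost. Calling these variables strong predictors, or counting the chance of a positive test among several candidate covariates, would go beyond a text that names only one. This is a wording change that should be made; it does not invalidate the trial.

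**What to change.** Replace the conditional clause in Statistical methods {20a} with:

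> The primary model will adjust for baseline Tanner stage and the sex/age randomisation categories in all cases, whatever the baseline comparison shows. Baseline characteristics will be described by arm without significance tests.

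Also state that baseline HOMA-IR enters either as a covariate or as a time point with a common baseline mean across arms. Apply the same rule to the secondary models, each with its own baseline value.

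The cost is small. All variables are already collected. The four sex/age categories use three degrees of freedom and Tanner stage uses one as a linear score (up to four as categories), against about 3 × 25.5 = 76 completers. Trial status reports that recruitment had not started at version 1.2, so on that footing the wording could be fixed before any data were seen.

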### Trial design {8}

A single-center, parallel three-armed, double-blinded, 12-month randomized controlled trial with a 1:1:1 allocation ratio. Ninety adolescents (*n* = 30 per arm) with obesity, IR, and family history of T2DM will be enrolled in the trial matched for sex and age (Figs. 1 and 2).

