## Interventions

### Explanation for the choice of comparators {6b}

We postulate that the therapeutic effects of both MET and fermentable fibers are mediated, in part, through diverging effects on the gut microbiome, and that MET plus fiber combination therapy will act synergistically to improve glucose tolerance in adolescents with obesity and IR. By combining MET with fiber, we anticipate that the improvement in IR and BMI will be significantly higher when compared to each monotherapy. A control group without treatment is not included, since a no treatment arm would be unethical for adolescents with obesity and IR.

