#### Methods for additional analyses (e.g., subgroup analyses) {20b}

We plan to do a subgroup analysis for age and sex differences within each arm.

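### A responder versus non-responder comparison cannot show which baseline microbiome features predict a treatment effect; an exploratory arm-by-feature interaction is needed, and it speaks only to contrasts between the active arms

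*Protocol article*

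**What the plan says.** All quotes are from the protocol article.

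- **Statistical methods {20a}, the analysis.** "Treatment responders versus non-responders will also be evaluated". The stated aim follows: "We will characterize the ecological differences prior to the intervention, and then the individualized response to the intervention in order to assess the role" (the role meant is that of gut bacteria in how each participant responds metabolically). The tool named is clustering: "we will apply a machine learning approach called partition around medoids clustering". It does not define response, and does not say whether arms are pooled or which data are clustered.
- **Statistical methods {20a}, the models.** "Intervention types and times will be included as fixed effects in linear mixed models". No baseline microbiome term and no arm-by-feature term is named. The OTU-level methods look for taxa that distinguish the treatment groups, and the correlations use changes in the microbiome, not baseline values.
- **Additional analyses {20b}.** "We plan to do a subgroup analysis for age and sex differences within each arm". This is the only effect-modifier analysis stated, and it does not concern the microbiome.
- **Discussion.** The microbiome work may lead to the "identification of baseline microbiota configurations or metabolites that predict effects of MET and/or fermentable fibers", which could then support personalized therapy.
- **Choice of comparators {6b}.** "A control group without treatment is not included".
- **Trial design {8}.** "Ninety adolescents (*n* = 30 per arm) with obesity, IR, and family history of T2DM will be enrolled". Allocation is 1:1:1.

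**The concern.** A baseline feature that predicts the effect of a treatment is one across whose levels the difference between randomized arms changes. A responder label describes something else: how far one person's value moved. If it rests on observed change in HOMA-IR, it carries the treatment effect together with ordinary within-person variation, pubertal change over 12 months at ages 12 to 18, and lifestyle change. The article treats pubertal stage as a possible confounder in {20a}, and its Discussion concedes that uncontrolled lifestyle changes can improve insulin resistance on their own.

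A feature linked to any of these will tend to differ between responders and non-responders even if every participant gains the same from treatment. Clustering around medoids does not help: it groups similar profiles and contains no treatment contrast.

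At stake is the reading of the results. A prognostic marker could be reported as a marker for choosing therapy, and a genuine modifier could be missed.

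**Working it through.** The article gives no figure for the responder analysis, so there is none to reproduce. The check asks what each analysis estimates, and then how often each flags a feature.

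**Inputs from the article.** Three arms, 30 per arm ({8}); 15% attrition ({14}), so 30 × 0.85 = 25.5, taken as 26 per arm.

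**Assumptions, not in the article.**
- Improvement in HOMA-IR, in SD units, is y = m(arm) + b·x + c·x·F + e.
- x is a standardized baseline feature, F = 1 in the two fiber-containing arms, and e is N(0,1).
- m = 0.75 in MET + FIBER and 0 in the other arms.
- Responder means above-median improvement.
- Tests are at two-sided 5%, one feature, with 4,000 simulated trials per setting.

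**What each analysis reads.**
- The slope of y on x is b in MET and b + c in MET + FIBER.
- The responder comparison within MET + FIBER responds to b + c. Pooled over three equal arms, it responds to roughly b + 2c/3.
- The interaction, MET + FIBER versus MET, responds to (b + c) − b = c.

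Only c concerns the treatment effect, and only the interaction isolates it.

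**Purely prognostic feature (c = 0), 26 per arm: share of trials with p < 0.05**

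| b | Responder comparison, pooled | Responder comparison, MET + FIBER only | Arm-by-feature interaction |
|---|---|---|---|
| 0 | 5% | 5% | 5% |
| 0.3 | 48% | 20% | 5% |
| 0.5 | 86% | 44% | 5% |
| 0.75 | 99% | 74% | 6% |

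Simulation error is about one percentage point; repeat runs differ by that order. With 30 per arm the responder shares are slightly higher (55%, 91% and nearly 100% pooled) and the interaction again stays near 5%.

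**True modifier hidden by an opposing prognostic effect (b = −0.5, c = 0.5), 26 per arm.** Within MET + FIBER the slope is −0.5 + 0.5 = 0, and the responder comparison flags the feature in 5% of trials. Pooled, the average slope is about −0.5 + 2(0.5)/3 = −0.17; the feature is flagged in 17%, with a sign opposite to the modification. The interaction detects it in 40%.

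**Power of the interaction, 26 per arm.**
- Standard error of the slope difference ≈ √(1/26 + 1/26) = 0.277.
- For c = 0.5: 0.5/0.277 = 1.80, and Φ(1.80 − 1.96) ≈ 0.44. Simulation gives about 41%.
- For c = 0.75, simulation gives about 71%.
- For a feature split 50/50 with an interaction of 0.75 SD: standard error √(4/13) = 0.555, 0.75/0.555 = 1.35, and Φ(1.35 − 1.96) ≈ 0.27.

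All of these are before any correction for testing many features.

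**The case against.** The case on the other side has real force.

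- **The setting is exploratory.** {20a} calls the secondary endpoints exploratory, and these include the microbiome outcomes. The Discussion says only that predictors may be found and could be used; it credits the microbiome analysis as a whole and does not mention the responder split. This stands: a reader might infer that the trial plans a firm claim of differential treatment effect, and the article does not. Exploratory status still does not turn a prognostic association into a predictor of effect.
- **The details may sit in a fuller plan.** This stands for the definition of response. That participants will be labelled by their own before-after change is an inference, though a natural one. The point rests instead on the method the article names and the inference it attaches to it.
- **Noise alone creates no false predictor.** This stands. A feature unrelated to outcome is flagged at the nominal 5% (first row of the table). The problem needs a feature that is truly prognostic, and the 0.3 to 0.75 SD range is assumed.
- **The share of apparent responders is not the size of the error.** Assuming a median HOMA-IR of 5, log SD 0.45 and test-retest correlation 0.5 to 0.8, some 24 to 35% of participants would fall by 20% or more with no treatment effect. It is tempting to read this as the error rate, or to blame the entry cut-off of 3.16. Neither holds: no microbiome feature enters that calculation, and without the cut-off the share is still 22 to 31%.
- **The remedy has limits too.** The missing untreated arm restricts the interaction as well, and power is low. Both stand and belong in the plan's wording.

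**Conclusion.** The point holds as a moderate one about an exploratory analysis. The responder comparison, with clustering that contains no arm contrast, cannot support the Discussion's hope of finding baseline features that predict effects of metformin or fiber, and no other stated analysis fills the gap. If a feature is prognostic at 0.3 to 0.75 SD, it is flagged in about 48 to 99% of trials pooled and 20 to 74% within one arm, against about 5% for the interaction. These figures rest on the assumed effects, an above-median definition of response, 26 per arm and one feature at a time.

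A reader might infer that an interaction would show who benefits from metformin, or from fiber, as such. The design does not allow that: every arm receives an active treatment, so neither monotherapy can be set against none. Nor does the point require dropping the responder description. The primary analysis is unaffected.

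**What to change.** 1. Keep the responder versus non-responder comparison, labelled as descriptive and hypothesis-generating.
2. Add an exploratory model of 12-month log HOMA-IR on arm, baseline log HOMA-IR, the baseline feature (or a cluster formed from baseline samples only) and arm-by-feature. Report the interaction estimates with confidence intervals and control multiplicity over the features tested.
3. Call a feature predictive only on the interaction; describe any other association with change as prognostic or undetermined.
4. State that, without an untreated arm, the interaction addresses modifiers of fiber added to metformin, of metformin added to fiber, or of metformin versus fiber, and not of either monotherapy against no treatment. Align the Discussion's wording with this.

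The cost is analysis wording and programming; the data and visits stay the same. The downside is imprecision: intervals will be wide, and power will fall further below the single-feature figures once multiplicity is controlled.
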